**10-1-4. Harmful signs related to symptoms and observations**

Symptoms and findings that newly develop after the first administration of the investigational drug, or symptoms and findings that were observed before the first administration of the investigational drug, but which the investigator determines to have worsened after the first administration of the investigational drug, shall be considered as adverse events related to symptoms and findings and entered in the case report form.

However, fluctuation of PS and appearance of new lesions shall not be treated as adverse events.

Aggravation of the underlying disease and complications resulting from it should be reported in accordance with "10-3-1. Serious Adverse Event Reporting Procedures" if they meet the definition of "10-1-3. In case of death, determine whether the cause is aggravation of the underlying disease or other reasons, e.g., due to the investigational drug.

**10-2. Survey items**

**10-2-1. Names of harmful events**

Enter the name of the symptom or diagnosis in the case of an adverse event related to symptoms and findings, and enter the name of the test item or the details of fluctuation in the case of an adverse event related to laboratory test values in the case report form.

**10-2-2. Date of onset (manifestation) and date of worst deterioration**

Enter the date and grade of onset and worst case. (The worst-case date is the date when the worst grade is first confirmed.) Enter the time of onset and worst case for acute infusion reaction or cytokine release syndrome.

**10-2-3. Severity of illness**

Grade should be determined according to CTCAE v4.0 and recorded in the case report form.

**10-2-4. Severity**

Select from the following codes.

1) Serious

2) Non-serious

**10-2-5. Treatment**

1) Treatment of investigational drug

Select from the following codes.

(1) No change

(2) Postponed

(3) Discontinued

(4) Not applicable

2) Other treatment (Enter the treatment method.)

Select the procedure other than the investigational drug from the following codes.

(1) None

(2) Reduction of concomitant medication

(3) Increase dose of concomitant drug

(4) Prescription of other drugs

(5) Other

**10-2-6. Outcome**

Describe the outcome confirmed by 4 weeks after the last observation period of the adverse event (16 weeks (28 weeks for Grade 3 or higher non-hematologic toxicity) after the last administration date of the study drug). Follow-up of adverse drug reactions (adverse events for which a causal relationship cannot be ruled out) will be conducted until they are confirmed to have recovered or become mild.

1) Recovery (when the patient returns to the same level as before the first administration of the investigational drug)

2) Slightly improved (the worst is over, but not back to the same level as before the first dose of the investigational drug)

3) Unrecoverable (the worst has continued)

4) Severe sequelae (the adverse event has resolved but other related symptoms remain)

5) Death (if the adverse event resulted in death)

6) Unknown (when the patient is unknown)

**10-2-7. Outcome date**

Enter also the date of outcome and grade confirmed by 4 weeks after the last observation period of the adverse event (16 weeks (28 weeks for non-hematologic toxicity of Grade 3 or higher) after the last administration date of the investigational drug). For acute infusion reactions or cytokine-releasing syndromes, the time of day should also be recorded.

**10-2-8. Causal relationship with investigational drug**

The following criteria should be used when determining the relevance of an investigational drug.

If the investigator determines that there is no association, the reason should be stated in the case report.

＜Criteria for determining the relevance of an investigational drug

1) No association

The adverse event is judged not to be related to the investigational drug because there is no reasonable possibility (time course between administration of the investigational drug and occurrence of the adverse event, pharmacological effects, etc.) within the scope of available information, and it can be judged that the adverse event has other causes such as aggravation of the primary illness.

2) May be related

After careful medical evaluation, the relationship between the event and the study drug administration is not certain or strongly suspected, but the existence of a causal relationship cannot be ruled out at all.

3) Possibly related

After careful medical evaluation, there is a high degree of certainty of a relationship between the event and the study drug administration.

4) Relevant

There is no doubt that the event occurred as a result of the administration of the investigational drug.

**10-3. Adverse event reporting and response**

Adverse events that must be reported are those that occur during the observation period of adverse events defined in "10-1-2. Definition of adverse events and adverse reactions (adverse events for which a causal relationship cannot be ruled out)" and "Serious adverse events" defined in "10-1-3. When such an adverse event occurs”, it should be reported in accordance with "10-3-1. Serious Adverse Event Reporting Procedures”.

In addition, if an adverse event that is not a serious adverse event but meets the criteria for DLT (defined in 8-3-1. Primary Endpoints) occurs in the Phase Ia portion, regardless of whether or not there is a causal relationship, the investigator should take appropriate measures, prepare a "Report on Adverse Events Related to Dose Increases" and promptly submit it to the Trial The report shall be promptly submitted to the Clinical Trial Coordinating Committee.

**10-3-1. Serious adverse event reporting procedures**

1) Immediate report (within 24 hours from the time of knowledge of the occurrence)

In the event of a reportable adverse event, the investigator shall take appropriate measures and report it to the head of the site, regardless of whether there is a causal relationship with the investigational drug or not, and shall immediately (within 24 hours from the time when he/she becomes aware of the occurrence) submit a "Report on Serious Adverse Events (Medical Form 12-1)" to the site's coordinating committee, stating the information available at that time. The information available up to that point shall be reported to the Clinical Trial Coordinating Committee.

2) Detailed report (within 3 days from the time when the investigator becomes aware of the occurrence)

The investigator shall prepare the "(Medical) Form 12-1, 2 Report on Serious Adverse Events" within 3 days of learning of the occurrence of a serious adverse event, and report it to the head of the investigational site as well as to the Clinical Trial Coordinating Committee. At that time, the relationship between the investigational drug and the adverse event should be fully considered. However, if the adverse event is a fatal or life-threatening serious adverse event for which a causal relationship with the unknown investigational drug cannot be denied, a detailed report shall be submitted to the TIC immediately (the next day at the latest). The TIC shall also immediately notify the investigators and investigational drug providers at other sites.

3) Response

The investigator who conducts the clinical trial himself/herself shall consider how to respond and take necessary measures under the coordination of the Clinical Trial Coordinating Committee. In case of administration of the investigational drug or discontinuation of the clinical trial, the investigator must promptly report to the Clinical Trial Coordinating Committee.

The TIC shall also request the Efficacy and Safety Evaluation Committee to deliberate and decide whether the clinical trial should be continued or not.

**10-3-2. Evaluation and recommendations by the effectiveness and safety assessment committee**

The Efficacy and Safety Evaluation Committee, which is requested to make an evaluation, shall review the contents of the "Report on Serious Adverse Events" and, if necessary, give instructions for detailed investigation after consultation with the Trial Coordinating Committee.

The Effectiveness and Safety Evaluation Committee will make an evaluation based on all information submitted and make recommendations to the Clinical Trial Coordinating Committee regarding the necessity of countermeasures and their contents. Possible measures include discontinuation of the clinical trial, interruption/continuation of enrollment/resumption of enrollment, modification of the clinical trial protocol, modification of the consent document, lot inspection of the investigational drug, provision of adverse event information to all investigational sites, and review by the Clinical Trial Review Committee.

**10-3-3. Determination of measures**

The person who conducts the clinical trial himself/herself shall make a decision on the necessity of countermeasures and their contents based on the recommendation from the Effectiveness and Safety Assessment Committee. The investigator who conducts the clinical trial himself/herself will inform the Efficacy and Safety Evaluation Committee, the Clinical Trial Review Committee, and the investigator himself/herself of the decision as necessary. When contacted by other sites, the investigator who conducts the clinical trial himself/herself will inform the Clinical Trial Review Committee of the contents of the countermeasures and the reasons for them, as necessary.

**10-4. Expected side effects**

(1) Skin disorders

A domestic Phase I clinical trial in patients with CCR4-positive relapsed/relapsed ATL and PTCL (Study No. 0761-0501), a domestic Phase II clinical trial in patients with CCR4-positive relapsed/relapsed ATL (Study No. 0761-002), a domestic late Phase II clinical trial in untreated patients with CCR4-positive first-episode ATL A late phase II study in Japan in patients with relapsed/relapsed CCR4-positive peripheral T/NK cell lymphoma (Study No. 0761-003), a late phase II study in Japan in patients with CCR4-positive relapsed/relapsed peripheral T/NK cell lymphoma (Study No. 0761-004), and a European phase II study in patients with CCR4-positive relapsed/refractory PTCL (Study No. 0761-007). During the 0761-002 study, two dermatologists attended a case review of dermatological symptoms with the attendance of two dermatologists. The committee agreed that "Stevens-Johnson syndrome" may have been caused by cytomegalovirus, but that adverse skin reactions other than "Stevens-Johnson syndrome" were caused by the pharmacological action of mogamulizumab. However, the investigators were of the opinion that adverse skin symptoms other than "Stevens-Johnson syndrome" were caused by the pharmacologic effects of mogamulizumab. The study concluded that these skin symptoms were not considered normal drug eruptions because they were not severe enough to be controlled with oral steroids or recovered spontaneously even if treatment was continued after the onset of skin eruptions. The adverse events of skin symptoms with mogamulizumab do not seem to be so harmful when compared with the efficacy of mogamulizumab. However, sufficient caution and appropriate treatment should be taken when skin symptoms occur due to the administration of mogamulizumab, and depending on the condition of skin symptoms, the administration of the investigational drug may be postponed and attention should be paid to the development of bacterial infections. From the launch of POTELIGEO® 20 mg for intravenous infusion (May 29, 2012) to February 28, 2013, three cases of toxic epidermal necrolysis in three patients and three cases of Stevens-Johnson syndrome in three patients were reported. One of the three patients developed sepsis and died. Therefore, on December 4, 2012, the company revised the instructions for use in the package insert regarding severe skin disorders, including toxic epidermal necrolysis and Stevens-Johnson syndrome.

(2) Injection-Related Reactions/Cytokine Release Syndrome and Tumor Decay Syndrome

Results of Study 0761-0501 and Study 0761-002 showed that, similar to other antibody drugs, "injection reactions" such as "fever," "chills," and "tachycardia" were frequently observed with mogamulizumab (overall incidence 86% (37/43 patients), of which Grade 3 The overall incidence was 86% (37/43 patients), of which Grade 3 or higher was 2% (1/43 patients)]. In the 0761-0501 study, "cytokine release syndrome" was observed in one patient. All events resolved spontaneously or with appropriate medical treatment, except for the subject who was deemed to have no further adverse events due to worsening of the underlying disease. Appropriate measures (e.g., infusion therapy, oxygen inhalation, steroid prescription, etc.) should be taken if symptoms develop.

In Study 0761-002, "Tumor Decay Syndrome" occurred in one patient (Grade 3). In the post-marketing surveillance of POTELIGEO® 20 mg for intravenous infusion (May 29, 2012 - November 28, 2012), one death due to "tumor collapse syndrome" was reported. Based on the above, due attention should be paid to the development of TLS due to rapid tumor cell destruction.

(3) Hematologic toxicity (lymphocyte count decreased, neutrophil count decreased, white blood cell count decreased, platelet count decreased)

Based on the above, adequate precautions against infection should be taken, and further, appropriate measures for infection prevention (e.g., anti-tuberculosis drugs, ST drugs, antifungal agents, etc.) should be taken if necessary.

**10-5. Action to be taken when adverse effects occur**

**10-5-1. Reactions associated with injection**

If an injection reaction is observed, immediately consider discontinuing administration or slowing down the administration rate, and promptly take appropriate measures according to the symptoms. 10-5-2.

**10-5-2. Skin disorder**

From the start of administration of this product, appropriate measures should be taken if any skin disorder is observed in collaboration with a dermatologist.

Since symptoms may progress rapidly and become severe in a short period of time, appropriate measures such as the use of a sufficient number of corticosteroids should be taken from the early stage of the onset of skin disorders. Corticosteroids should be considered for oral administration from the Grade 2 stage. Especially in cases of mucocutaneous disorders or when symptoms are ongoing, a sufficient dose (1 mg/kg prednisolone equivalent) should be used from the early stages of administration, and steroid pulse therapy should be administered in some cases.

If complications are observed, the skin disorder should be addressed while taking measures to deal with the complications.

If the skin disorder is ongoing, defer administration of the drug until the condition resolves.

If the skin disorder is Grade 2 or less and is controlled with corticosteroids at moderate doses (0.5 mg/kg prednisolone equivalent) or lower, consider continuation of the drug without deferral.

If Grade 3 or higher skin disorders occur, discontinue administration of the drug and take appropriate measures. Skin lesions caused by this drug may appear not only on visible areas such as the extremities, but also on the back, chest, and other parts of the body hidden by clothing. Also, since toxic epidermal necrolysis and Stevens-Johnson syndrome generally have mucocutaneous symptoms and may be preceded by mucocutaneous symptoms, the eyes, oral cavity, anus, vulva, and other skin-mucosal transition areas should also be checked.

Since severe skin disorders have been reported to occur not only during treatment with the drug but also several weeks after the end of treatment, patients should continue to be monitored regularly for their general skin condition after the end of treatment.

The recommended measures for each Grade are shown in Appendix 1.

**10-5-3. Hepatitis B virus hepatitis**

If any abnormality is observed, administration of this drug should be discontinued, and appropriate measures such as administering antiviral drugs should be taken immediately.

**10-5-4. Tumor lysis syndrome**

If any abnormality is observed, administration of this drug should be discontinued immediately, and appropriate measures (e.g., administration of saline solution, hyperuricemia treatment, dialysis, etc.) should be taken and patients should be carefully monitored until symptoms recover.

**10-5-5. Hematotoxicity and liver dysfunction**

If any abnormality is observed, appropriate measures such as postponement or discontinuation of administration of the drug should be taken.

**10-6. Measures to be taken if pregnancy is confirmed**

If a subject becomes pregnant, the investigator shall immediately discontinue administration of the investigational drug and report to the Clinical Research Coordinating Committee in accordance with the "Procedures for Handling Safety Information" separately stipulated. The Clinical Research Coordinating Committee shall immediately report to the investigational drug provider. Pregnancy itself is not considered an adverse event unless it is suspected that the investigational drug interfered with the effectiveness of the contraceptive. However, all pregnancies (including cases in which the subject discontinues the clinical trial), the outcome of pregnancy (spontaneous abortion, artificial abortion, normal delivery or delivery with congenital abnormality) shall be followed up and recorded. Birth defects, birth defects, and spontaneous abortions must be reported as serious adverse events. Uncomplicated abortions are not treated as adverse events. All pregnancy outcomes shall be reported to the Clinical Research Coordinating Committee, which shall submit them to the investigational drug provider.

**10-7. Measures in case of overdose**

If an overdose is administered to a subject, it shall be reported to the Clinical Trial Coordinating Committee in accordance with the "Procedures for Handling Safety Information" separately stipulated. The TIC shall promptly report it to the investigational drug supplier.

**11. Statistical analysis**

**11-1. Analysis population**

1) Safety Analysis Population

For each of Phase Ia and Phase Ib, the population shall consist of subjects who satisfy all of the following conditions

(1) Subjects who do not fall into the category of serious GCP non-compliance cases such as failure to obtain appropriate informed consent.

(2) Subjects who have received at least one dose of the investigational drug

2) Efficacy analysis population (Full Analysis Set)

The Full Analysis Set shall be the population of subjects who satisfy all of the following conditions for each of Phase Ia and Phase Ib.

(1) Subjects who do not fall into the category of serious GCP non-compliance cases such as failure to obtain appropriate informed consent

(2) Subjects who have received at least one dose of the investigational drug

(3) Subjects who have evaluation data after receiving the investigational drug

3) Pharmacokinetic analysis population

Subjects in Phase Ia of the safety analysis population.

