**9-4-3. CT and MRI**

Measurements will be taken at baseline and at Week 12. Thereafter, it will be performed every 12 weeks. It will also be performed every 12 weeks after discontinuation of the investigational drug if possible, and measurements will be taken at the time of discontinuation of the study.

The CT or MRI scan should be performed using the same model at each site and under the same imaging conditions for each subject as far as possible.

The cases judged as CR or PR by the RECIST method are objectively and uniformly judged by the Central Evaluation Committee of Imaging, which is a third-party organization.

The investigator submits the image data of cases judged as CR or PR to the Central Radiological Evaluation Committee at an appropriate time in accordance with the "Procedures for Central Radiological Evaluation," which is separately stipulated. If the judgment of the investigator and that of the Central Radiological Evaluation Committee differ, the judgment of the Central Radiological Evaluation Committee shall be the final evaluation.

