**11-4. Analysis items and methods**

Detailed analysis methods are described in the "Statistical Analysis Plan" and "Pharmacokinetic Analysis Plan" to be prepared separately.

1) Safety

(1) Number of DLT cases

The number of DLTs and the incidence rate of DLTs per treatment group in Phase Ia are shown.

(2) Occurrence of adverse events and adverse reactions

Adverse events that occurred in Phase Ia and Phase Ib are summarized in the table. All adverse events and adverse drug reactions are summarized by the MedDRA basic terms and by major organ category, and the number and percentage of adverse events for each treatment group are shown.

(3) Gene analysis

Exploratory studies will be conducted as necessary.

2) Efficacy

(1) Efficacy in eliminating regulatory T cells

Summary statistics are calculated for each treatment group.

(2) Antigen-specific antibody immune response

To be investigated in an exploratory manner for each treatment group.

(3) Anti-tumor effect

The number of responders and the percentage of responders (response rate) will be calculated for each treatment group.

(4) Progression-free survival (PFS)

Progression-free survival is calculated using the Kaplan-Meier method.

(5) Overall survival (OS)

Overall survival is calculated using the Kaplan-Meier method.

(6) Immunostimulatory effect

To be examined on an exploratory basis as necessary.

(7) Gene analysis

To be explored as necessary.

In addition, the relationship between regulatory T-cell elimination effect and anti-tumor effect, antigen-specific antibody immune response, etc. will be explored.

3) Pharmacokinetics

(1) Plasma Mogamulizumab concentration

Plasma concentrations of Mogamulizumab will be listed and descriptive statistics for each dose will be shown; plasma concentration trends of Mogamulizumab will be plotted graphically as individual subject data and mean (+ standard deviation) versus blood collection time on a real and log scale.

(2) Mogamulizumab pharmacokinetic parameters

Calculate the pharmacokinetic parameters for each subject as indicated in "8-3-1 Definition of primary endpoints 1) Phase Ia Part (2) Pharmacokinetics" and calculate descriptive statistics for each dose.

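### The only efficacy population requires undefined post-dose evaluation data, so treated patients lost very early can leave the response denominator and, on a narrow reading, the PFS and OS curves

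*Protocol*

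**What the plan says.** Section 11-1 defines a safety population and one efficacy population for each phase. Both exclude serious GCP non-compliance, and both carry the condition "2) Subjects who have received at least one dose of the investigational drug". The efficacy population alone adds "3) Subjects who have evaluation data after receiving the investigational drug". Section 11-2 labels cases with incomplete evaluation data but does not say whether they are kept.

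Section 11-4 names no other population for the efficacy summaries:

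- Response: "The number of responders and the percentage of responders (response rate) will be calculated for each treatment group".
- PFS: "Progression-free survival is calculated using the Kaplan-Meier method".
- OS: "Overall survival is calculated using the Kaplan-Meier method".

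On timing, section 9-4-3 says of CT and MRI: "Measurements will be taken at baseline and at Week 12. Thereafter, it will be performed every 12 weeks". The first post-dose regulatory T-cell and antibody samples are due at Week 5 (sections 9-4-1 and 9-4-2).

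Section 8-3-2 gives event rules that need no scan. Rapid worsening that prevents examination counts as progression on the date it is clinically evident. Death before confirmed progression is a PFS event whatever its cause. OS runs from first dose to death from any cause. Phase Ib uses the same definitions by cross-reference.

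**The concern.** The first two conditions are those of the safety set, so the third can do only one thing: remove dosed, GCP-compliant patients from the efficacy analyses. Those most likely to have no post-dose assessment are patients who die or leave very early. Entry allows ECOG performance status up to 2 and asks for an expected survival of only 3 months (section 4-1), about the time of the first scan. Missing data are then related to outcome, and the excluded patients cannot be responders.

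At stake is the accuracy of the response rate, and possibly of the PFS and OS curves, in groups of 20. When Phase Ib has two groups they are randomised by minimisation (section 7-5-2), so the condition also selects on something observed after randomisation.

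**Working it through.** The protocol gives no power, event or dropout figure to reproduce; section 7-6-2 sets 20 per group by whether the regulatory T-cell effect can be studied and by feasibility. The check has three parts: who can be lost, how far the estimates move, and whether the rules agree.

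**1. Who can be lost depends on the reading of evaluation data**

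| Reading | Patients exposed to exclusion |
|---|---|
| Tumour imaging only | No scan, mainly those lost before Week 12 |
| Any efficacy test | Lost before about Week 5 with no sample at discontinuation |
| Any post-dose data, including survival status | Almost none |

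For scale, assume exponential survival with median *m* weeks. The first dose is Week 1, so Week 5 is 4 weeks and Week 12 is 11 weeks after it. Expected deaths per 20 are 20 × (1 − 0.5^(t/m)). These medians are assumptions; the protocol gives none for this population.

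| Assumed median OS | Deaths before Week 5 | Deaths before Week 12 |
|---|---|---|
| 3 months | 3.8 | 8.9 |
| 6 months | 2.0 | 5.1 |
| 9 months | 1.4 | 3.5 |
| 12 months | 1.0 | 2.7 |

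These are deaths, not exclusions. A sample or scan taken at discontinuation would keep some of these patients in the set.

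If a share *p* of treated patients has no qualifying data, the chance that a group of 20 loses at least one is 1 − (1 − p)^20. For p = 5%, 10%, 15% and 20% this is 64%, 88%, 96% and 99%.

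**2. How far the estimates move**

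With *r* responders and *k* patients excluded, the reported rate is r/(20 − k). An excluded patient is not a responder, so *r* stays fixed and the rate cannot fall. Both counts are assumptions.

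- r = 3: 3/20 = 15.0%; k = 1 gives 3/19 = 15.8%; k = 3 gives 3/17 = 17.6%.
- r = 4: 4/20 = 20.0%; k = 1 gives 4/19 = 21.1%; k = 4 gives 4/16 = 25.0%.

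Sampling error is larger. The exact 95% interval for 4/20 is 5.7% to 43.7%. The same method gives 29.9% to 70.1% for 13/26, matching the interval in section 1-3-2-2 for the earlier ATL Phase II study.

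If early deaths are also dropped from the time-to-event analyses, and there is no earlier censoring:

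- OS at Week 12: 16/20 = 80% becomes 16/19 = 84.2% with one early death removed and 16/16 = 100% with four.
- PFS at Week 12: 10/20 = 50% becomes 10/19 = 52.6% with one early event removed and 10/16 = 62.5% with four.

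An early withdrawal without an event would be censored near the start, so dropping it barely moves these curves.

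**3. Whether the rules agree**

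Section 8-3-2 gives an event to a patient who dies, or clearly worsens, without ever being scanned. Section 11-1 admits that patient only if the death or clinical progression date counts as evaluation data, and no section says that it does. If it does not, one rule supplies an event for a patient whom the other removes. For response, no rule counts an unassessed patient as a non-responder.

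**The case against.** The strongest reply is that the condition does not mention imaging. The set serves every efficacy endpoint, and blood for the Week 5 tests is also drawn when dosing is discontinued, so on an ordinary reading few patients have nothing. This stands. A reader might infer that everyone without a Week 12 scan is excluded; the text does not support that.

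A reader might also infer that patients who stop for toxicity are removed. Stopping drug does not stop evaluation: blood is drawn at discontinuation, imaging continues every 12 weeks if possible and is due at study discontinuation, and survival is followed (sections 9-4-1 to 9-4-4). Section 14-1-2 ends evaluation only for withdrawal of consent, death, non-attendance or the investigator's decision. This too stands.

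Nor can it be said that PFS and OS will lose their earliest events. Section 8-3-2 shows an intention to count them, so the loss occurs only on the narrow reading.

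The sizes are assumed. In the ATL Phase II study 27 patients were treated and 26 analysed for efficacy, but no reason is given, so this is not evidence about missing evaluations.

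Finally, section 11-4 leaves detailed methods to a separate analysis plan. That answers a complaint about a missing definition. It does not answer this point, because the population rule is written in the protocol and can act only by removing treated patients.

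**Conclusion.** The point holds in a limited form. Treated patients with no qualifying post-dose assessment, mainly very early deaths and withdrawals, can leave the response denominator, and the response rate can then only be raised. Response is affected most clearly. PFS and OS are affected only if a recorded death or clinical progression date is not evaluation data, a reading that contradicts section 8-3-2.

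With one to three of 20 excluded and three responders, the rate moves from 15.0% to between 15.8% and 17.6%, which is small beside the sampling error. All of these counts are assumptions.

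A reader might go further and conclude that the randomised comparison or the recommended dose is compromised. The protocol does not support that. Response, PFS and OS are secondary, section 11-4 states no test between doses, and section 8-3-2 bases the recommended dose on safety and regulatory T-cell elimination. Safety is analysed in all treated, GCP-compliant subjects. The harm is possible upward bias in descriptive secondary estimates, which is worth correcting because the correction is cheap.

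**What to change.** Amend section 11-1 as follows:

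- Analyse response, PFS and OS in all treated, GCP-compliant subjects, by assigned dose when Phase Ib is randomised.
- Count a subject with no post-baseline tumour assessment as a non-responder.
- Keep the section 8-3-2 event rules for PFS and OS unchanged.
- Apply the third condition only to regulatory T-cell change from baseline, which cannot be computed without a post-dose sample, and say there which data qualify.

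This is a short text change. It needs no extra patients, visits or data and leaves the regulatory T-cell analysis as it is. Its cost is that the reported response rate may be slightly lower. It settles the matter whichever reading was intended.
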